# The efficacy and safety of *Jiedu Tongluo* granules for treating post-stroke depression with *qi* deficiency and blood stasis syndrome: study protocol for a randomized controlled trial

**DOI:** 10.1186/s13063-018-2633-4

**Published:** 2018-05-10

**Keywords:** *Jiedu Tongluo* granules, Post-stroke depression, Randomized controlled trial, Chinese herbal medicine, *Qi* deficiency and blood stasis syndrome

## Abstract

**Background:**

Post-stroke depression (PSD) is the most common psychiatric complication after a stroke. The most frequently used antidepressants are selective serotonin receptor inhibitors (SSRIs) and serotonin and norepinephrine reuptake inhibitors (SNRIs), however, these exhibit a series of side effects. Traditional Chinese medicine has been used to treat PSD with few side effects. The aim of this study is to evaluate the efficacy and safety of *Jiedu Tongluo* granules for treating PSD with *qi deficiency* and *blood stasis syndrome*.

**Methods:**

The planned study is a double-blind, randomized, placebo-controlled pilot trial. Eighty participants will be randomly assigned to receive either treatment or placebo. The treatment group will receive *Jiedu Tongluo* granules (JDTLG) with conventional treatment, and the placebo group will receive placebo with conventional treatment for 8 weeks. The primary outcome is the effectiveness of JDTLG on depression after 8 weeks treatment, which is defined as a decrease of 50% or more in 17-item Hamilton Depression Scale (HAMD-17) score or clinical recovery (score < 7). Secondary outcomes are improvement in neurological function, degree of independence, activities of daily living, and TCM syndrome at each visit, which will be measured with National Institute of Health Stroke Scale (NIHSS), modified Rankin Scale (mRS), Barthel Index (BI) and TCM scale, respectively. Interleukin (IL)-6, IL-8, and small-molecule metabolites will be monitored to explore the mechanism of action of JDTLG on PSD. Safety measures include vital signs, results of electrocardiography, laboratory index (full blood count, kidney and liver function tests) and adverse events.

**Discussion:**

The purpose of this trial is to evaluate the therapeutic effects and safety of JDTLG in individuals with PSD with concomitant *qi deficiency* and *blood stasis syndrome*. If successful, the outcome of this trial will provide a viable treatment option for PSD patients.

**Trial registration:**

ClinicalTrials.gov ID: NCT03147053. Registered on 27 April 2017.

**Electronic supplementary material:**

The online version of this article (10.1186/s13063-018-2633-4) contains supplementary material, which is available to authorized users.

## Background

Post-stroke depression (PSD) is one of the most common complications of stroke and is characterized by depressed mood, generalized anxiety, and apathy [1–3]. The prevalence of PSD is approximately one third of stroke survivors at any one time [4], ranging from 39% to 52% within the first 5 years [5]. PSD patients experience poor functional outcomes [6] and increased mortality [7]. Several therapeutic strategies have been shown to be effective for PSD, including pharmacological, non-pharmacological interventions (e.g., psychotherapy, electroconvulsive therapy, and acupuncture), and combination therapies [8]. The most frequently studied agents are antidepressants, whereby the most thoroughly characterized agents are selective serotonin reuptake inhibitors (SSRIs) (e.g., fluoxetine, sertraline, citalopram) and serotonin and norepinephrine reuptake inhibitors (SNRIs) [9]. However, antidepressant medications exhibit a series of side effects, such as increased risk of hemorrhagic complications and stroke [10], although minor side effects such as nausea, diarrhea, fatigue, and dizziness are most commonly reported.

Traditional Chinese medicine (TCM) has been used to treat PSD and has demonstrated a more favorable safety profile than conventional medicine. A meta-analysis showed that *Liver-qi* regulation effectively ameliorates depressive symptoms, as well as enhancing quality of life among patients with PSD [11]. According to a data from a previous  research about the syndrome differentiation of ischemic stroke, the syndrome of *“qi deficiency* and *blood stasis”* might reach a proportion of 21.54% among the clinical patients, which would rank first within the different subtypes [12]. As a common complication of stroke, PSD can be divided into different syndromes, among which qi deficiency and blood stasis is an important subtype [13, 14]. *Jiedu Tongluo* granules (JDTLG) is a patented complex Chinese medicine formulation (No: 201510419571.3), which consist of seven herbs, including *Panax ginseng* (*Ren Shen*) 12.5 g/100 g, *Ginkgo biloba* (*Yin Xing Ye*) 25 g/100 g, *Hypericum perforatum L.* (*Guan Ye Lian Qiao*) 12.5 g/100 g, *Scutellaria baicalensis Georgi* (*Huang Qin*) 12.5 g/100 g, *Gardenia jasminoides Ellis* (*Zhi Zi*) 12.5 g/100 g, *Gastrodia elata Bl.* (*Tian Ma*) 12.5 g/100 g, and *Ligusticum chuanxiong hort* (*Chuan Xiong*) 12.5 g/100 g. According to the TCM theory, these herbs are believed to supplement *qi* and activate blood circulation, remove toxins and relieve stagnation, extinguish *wind*, and dredge collaterals. One previous study showed that JDTLG significantly improved depression-like behavior in animal stroke models [15]. *Panax ginseng* and *Ginkgo biloba*, key components of JDTLG, are known to possess neuro-protective effects [16–20]. Furthermore*, the antidepressant effects of Panax ginseng* [21] and *Ginkgo biloba*’s [22] might be derived from activation of the signaling pathway involving brain derived neurotrophic factor (BDNF). Our preclinical pharmacological experiments have shown that JDTLG has a neuroprotective and anti-apoptotic effect via up-regulating the expression of BDNF, hypoxia-inducible factor 1-alpha (HIF1α), cAMP-response element binding protein (CREB) and reducing the expression of vascular cell adhesion molecule1 (VCAM1) and matrix metallopeptidase 9 (MMP9). In addition, JDTLG can exert an anti-depressant function through increasing the expression of tropomyosin receptor kinase B (TrkB), mammalian target of rapamycin (mTOR), and 5-hydroxytryptamine (5-HT) receptor (unpublished data).

This study aims to explore whether JDTLG can improve depression and daily living compared with placebo in PSD participants with qi deficiency and blood stasis syndrome.

## Methods/design

### Study design

This is a double-blind, randomized, placebo-controlled, pilot trial designed to evaluate the safety and efficacy of JDTLG in treating PSD with qi deficiency and blood stasis syndrome. Eighty participants with PSD will be recruited from Xiyuan Hospital of China Academy of Chinese Medical Sciences. After obtaining written informed consent from participants or their legal guardian, participants will be randomly assigned to either the treatment or placebo group with a ratio of 1:1. Participants will undergo an 8-week treatment period and an 8-week follow up. The protocol design is based on the Consolidated Standards of Reporting Trials (CONSORT) guidelines and Standard Protocol Items: Recommendations for Interventional Trials (SPIRIT) Checklist (see Additional file 1).

### Recruitment

Participants will be recruited by Internet advertisement and posters in the community and selected hospitals. Potential participants will be assessed by an attending trial physician who will determine whether the participant meets the eligibility criteria. The physician will explain the study’s aims, procedures, and possible side effects of participation in detail and provide the participant with a copy of the Participant Information Sheet. The recruitment started in April 2017 and is estimated to end in March 2018. If the potential participant is eligible and interested in participating, they will be invited for a baseline screening prior to randomization. An outline of procedures is illustrated in Fig. 1.

**Fig. 1 Fig1:**
[figure not shown]
Study outline

### Diagnostic criteria

A diagnosis of stroke will be established according to *all kinds of cerebrovascular disease diagnosis points* [23]. Clinical diagnosis of depression is based on the *Chinese Classification and Diagnostic Criteria of Mental Disorders-3* (CCMD-3) [24] and the *Diagnostic and Statistical Manual of Mental Disorders-IV* (DSM-IV). The TCM syndrome of qi deficiency and blood stasis in the study follows the *Guidelines for Clinical Research of New Chinese Medicine* [25]*.* The diagnostic standards are as follows:Primary signs and symptoms include hemiplegia, tongue skew, tongue strong with no words, partial numbness or feeling diminished or disappeared, emotional depression or anxietySecondary signs and symptoms include dizziness, shortness of breath, dark lips, and pale tongue with petechial ecchymosis, string slide pulse

In the diagnosis of stroke involving both collateral and meridian, participants will be diagnosed with qi deficiency and blood stasis syndrome under condition of two or more primary signs/symptoms, as well as at least two primary signs/symptoms.

#### Inclusion criteria

Clinical diagnosis of stroke, showing symptoms of neurological deficitClinical diagnosis of depression according to the DSM-IV or CCMD-3A score of 7–24 on the 17-item Hamilton Depression rating scaleAbsence of psychiatric disease history or family history of psychosis before strokeConscious and cooperative, without aphasia or severe cognitive impairment 2 weeks after strokeHormones or psychotropic drugs not used within 1 month prior to enrollmentNormal liver and renal function testsAged 45–80 years oldDiagnosis of qi deficiency and blood stasis syndrome according to TCM pattern diagnosisAble to provide voluntary signed informed consent

#### Exclusion criteria

Suspected secondary stroke caused by brain tumor, brain traumaUnstable vital signs, or presence of severe primary hepatic or renal insufficiency (defined as the alanine aminotransferase (ALT), or the aspartate aminotransferase (AST), the serum creatinine concentration value twice of the normal upper limit)Presence of other chronic disorders (e.g., chronic alcoholism or drug abuse)Poorly controlled diabetes (the preprandial blood glucose is twice the upper limit of normal)Currently pregnant or breast-feedingAllergy to the ingredients in JDTLGCurrently participating in another clinical trial

### Withdrawal and discontinuation

Participants are able to voluntarily withdraw at any time during the trial. Participants who fail to complete the study, regardless of time or reason, will be considered as dropouts. The last recorded data for these participants will be included in data analyses. Data obtained from participants who experience unrelated complications, such as substantial change in disease status, exacerbation of depression or commence medication that could potentially interfere with JDTLG, will be treated as invalid. Withdrawal due to adverse events will be distinguished from withdrawal due to insufficient response. All adverse effects will be analyzed at the endpoint of the trial regardless of whether they are deemed related to the trial medication or not. If a participant withdraws due to a serious adverse event, it will be reported in accordance with the reporting requirements. Where appropriate, data collected by these participants will be used in intention-to-treat analyses.

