### Intervention

Participants will be allocated to receive JDTLG or placebo for 8 weeks in addition to their usual conventional treatment (e.g., antiplatelet, lipid-lowering, antihypertensive, or antidiabetic therapy). The JDTLG and placebo granules (3.9 g/sachet) will be taken orally with warm water twice a day for 8 weeks. Product will be provided by China Resources Sanjiu Medical and Pharmaceutical Co., Ltd., Shenzhen, China (Production batch number: 161001 W). Analyses have shown that the quality of JDTLG is consistent with the Chinese Medicine Standards of the State Food and Drug Administration (SFDA). Active granules contain 3.9 g of JDTLG each, which is equivalent to 24 g of crude medicine. Placebo granules are composed of 10% crude JDTLG and 90% starch and are of identical appearance and smell as the active granules. Participants will be instructed to refrain from all other Chinese herbal decoctions or medicines used to treat PSD during the study. Participants can withdraw from the study and choose modern medical treatments, such as SSRI antidepressants, when their depressive symptoms worsen. All of the unused granules will be asked to be returned to the trial team and reasons of not taking the medicine will be recorded on the CRF.

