### Outcomes and measures

#### Primary outcome

The primary outcome is the effectiveness of JDTLG on reducing depression after 8 weeks of treatment. Efficacy defined as a decrease of 50% or more in the 17-item Hamilton Depression Scale (HAMD-17) score or clinical recovery (score < 7) [26].

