### Study visits and procedures

The visit schedule for all evaluations (baseline, primary outcomes, secondary outcomes, exploring outcomes and safety indicators) is shown in Table 1. Participants will be assessed by the same investigator at each assessment. Baseline measurements, demographic characteristics, and medical history will be collected at the first visit only. All concomitant medications will be recorded during the treatment period (i.e., baseline to 8 weeks), including the name, dosage, and course of these medications. Primary and secondary outcomes and safety indicators will be collected every 4 weeks from baseline until week 16.

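### A dropout's last recorded score stands in for week 8, so a week-4 responder who leaves counts as effective, while data from participants who worsen are discarded

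*Protocol article*

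**What the plan says.** All of the following is in the protocol article.

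- Withdrawal and discontinuation defines the group: "Participants who fail to complete the study, regardless of time or reason, will be considered as dropouts". It then gives the rule for their data: "The last recorded data for these participants will be included in data analyses".
- The next sentence of that section gives a different rule for some participants. Data from those with, among other events, "exacerbation of depression or commence medication that could potentially interfere with JDTLG, will be treated as invalid".
- The section ends with a qualifier that has no criterion: "Where appropriate, data collected by these participants will be used in intention-to-treat analyses".
- Primary outcome fixes the time point: "The primary outcome is the effectiveness of JDTLG on reducing depression after 8 weeks of treatment". Response means at least a halving of HAMD-17 or a score below 7.
- Study visits and procedures fixes the schedule: "Primary and secondary outcomes and safety indicators will be collected every 4 weeks from baseline until week 16".
- Intervention gives one route out of the trial: "Participants can withdraw from the study and choose modern medical treatments, such as SSRI antidepressants, when their depressive symptoms worsen".
- Statistical analysis bases outcomes on intention-to-treat. It compares responders by Pearson's chi-squared test, with logistic regression for adjustment.

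No other rule for a missing week-8 score is given.

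**The concern.** The primary question is whether a participant is better after 8 weeks of treatment. For someone who left between weeks 4 and 8, the stated rule answers it with the state at week 4. A participant who stopped because the granules were not tolerated can then be credited with their benefit. The substituted score also enters the chi-squared test as if it had been observed.

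The neighbouring sentence makes this worse. On a plain reading, participants who deteriorate or start interfering medication drop out of the data, although they are the likeliest failures. Other leavers keep a possibly favourable week-4 score. The two sentences treat leavers unequally according to outcome, and the second does not fit an intention-to-treat analysis.

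The article is not silent here. It states a rule, so this cannot be set aside as detail left to an analysis plan. The trial is a pilot, but Sample size calculation says its results will be used to size later studies, so distorted response rates would carry over.

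**Working it through.** **No stated figure to reproduce.** The article gives no alpha, power, response rate or dropout rate. Only 40 + 40 = 80 can be checked, and it agrees. All rates below are assumptions.

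**Step 1: who is affected.** Visits fall at weeks 0, 4, 8, 12 and 16.

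- Leaves before the week-4 visit: the last score is baseline, 7-24 under the inclusion criteria. It is neither a 50% fall nor below 7, so the participant is a non-responder.
- Leaves between weeks 4 and 8: the week-4 score is used. If it met the rule, the participant counts as effective at week 8.
- Leaves after the week-8 visit: a real week-8 score exists.

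Only the middle group matters.

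**Step 2: how easily week 4 can qualify.** A baseline of 7 reaches a score below 7 with a 1-point fall, a baseline of 8 needs 2 points, and a baseline of 10 needs 4. Near the entry threshold, an ordinary fluctuation at week 4 can be fixed as a week-8 response.

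**Step 3: effect on each arm.** The comparison is with counting these leavers as non-responders.

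Extra responders = n × (share leaving in weeks 4-8) × (share of them responding at week 4)

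With n = 40, 15% leaving and 30-40% responding: 40 × 0.15 × 0.30 = 1.8, and 40 × 0.15 × 0.40 = 2.4. Divided by 40, that is 4.5 to 6 points per arm.

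**Step 4: effect on the treatment difference.**

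Shift = (active leaving share − placebo leaving share) × (week-4 response share)

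- 15% in both arms: (0.15 − 0.15) × 0.30-0.40 = 0.
- 20% active, 5% placebo: 0.15 × 0.30-0.40 = +4.5 to +6 points.
- 5% active, 20% placebo: −0.15 × 0.30-0.40 = −4.5 to −6 points.

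This assumes the same week-4 response share among leavers in both arms.

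**Step 5: a second illustration.** Assume completer response of 50% active and 30% placebo, and 0-50% of leavers responding at week 4.

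| Leavers, active / placebo | Difference, leavers as non-responders | Difference, last score used |
|---|---|---|
| 4 / 4 | 18.0 | 18.0 |
| 8 / 4 | 13.0 | 13.0 to 18.0 |
| 4 / 8 | 21.0 | 16.0 to 21.0 |

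**Step 6: sensitivity to one participant.** One participant is 1/40 = 2.5 points. With assumed counts, 21 versus 12 responders gives p = 0.041 and 20 versus 12 gives p = 0.068 (Pearson, no continuity correction).

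**Step 7: the discard rule.** Removing a non-responder shrinks the denominator. With 20 responders, one removal changes 20/40 = 50.0% to 20/39 = 51.3%. Steps 3-5 leave this out; they treat all late leavers as carried forward.

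**The case against.** Three stronger readings are tempting, and the article does not support them.

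- *A week-4 responder who leaves for antidepressants is scored effective at week 8.* The sentence on invalid data probably covers this case, since it names worsening and interfering medication. Such data would be discarded, not carried forward. The carry-forward problem is therefore clearest for adverse-event and voluntary leavers.
- *Data collection stops at dropout.* The article does not say so. Leaving the study may suggest it, but outcomes are scheduled to week 16, and Table 1 is not shown, so an early-withdrawal rating cannot be ruled out. For the same reason, week 4 is the only earlier post-baseline score among scheduled visits, not necessarily the only one.
- *The rule favours the granules.* Step 4 shows zero, positive or negative shifts. Participants may leave on worsening, so higher placebo dropout is plausible, and that would shrink the difference.

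Other points also have force. The words last observation carried forward do not appear, and the closing qualifier leaves room for judgement. Non-responder counting is itself a convention, not the truth. The article also uses the word invalid for the lowest TCM response category, so the disputed sentence might mean counted as failures. However, its subject is data, not outcome, and the plain reading is exclusion. Imputation detail is ordinary analysis-plan content, and the trial is exploratory and declared not fully powered.

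None of this removes the core. A rule covering all dropouts, a week-8 responder endpoint and intention-to-treat, with no other provision, lead to single substitution of the last score. The qualifier gives no criterion for doing otherwise.

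**Conclusion.** The point holds in a limited form. The dropout rule lets week-4 response stand in for week-8 response in adverse-event and voluntary leavers between those visits. The next sentence conflicts with that rule's universal scope and with intention-to-treat, and as written it removes likely failures.

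The size is conditional. Under the assumed 15% late dropout and 30-40% week-4 response, each arm's rate is 4.5-6 points above non-responder counting and the difference is unchanged. Under 20% versus 5%, the difference moves 4.5-6 points towards whichever arm loses more participants. Few or no late leavers would make the effect negligible.

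This should be corrected, but it does not undermine the design. In a pilot of 40 per arm, the main harm is to the response rates passed on to the next trial's sample size.

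**What to change.** For the primary outcome, replace the two conflicting sentences, and the undefined qualifier, with one intention-to-treat rule:

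1. All randomised participants are analysed, and none are discarded as invalid.
2. Those who withdraw for lack of effect, worsening, start of antidepressants or an adverse event count as non-responders. The article already plans to distinguish adverse-event withdrawal from insufficient response; the other reasons need recording in the same way.
3. HAMD-17 is still collected at scheduled visits after the granules stop, where the participant agrees.
4. Week-8 values missing for other reasons are multiply imputed, using baseline and week-4 HAMD-17.
5. A sensitivity analysis counts every missing week-8 value as non-response.

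This concerns analysis and data collection only; it does not change who may leave or what treatment they may take. The cost is revised wording, a small imputation step, some effort to rate participants who have stopped (the visits already exist), and slightly lower reported response rates.

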### Statistical analysis

All of the data from this study will be analyzed by biostatisticians using SPSS 20.0 (IBM Corp., Armonk, NY, USA). Outcomes are based on the intention-to-treat analysis.

Baseline characteristics will be summarized by means of simple descriptive statistics and be compared between two study groups to assess covariate balance. The two-sample Student’s *t* test will be used for continuous variables and the chi-square test or Wilcoxon test will be used for categorical variables.

The primary analysis will be a comparison of the efficacy on depression between the two groups after 8 weeks of treatment. Pearson’s chi-squared test will be used to analyze the effective cases and logistic regression will be used to adjust for chance imbalances in the main prognostic variables between groups, such as age and gender.

Secondary analyses will include the improved cases in neurological function (NIHSS score reduction of ≥ 50% or the total score of 0–1), independence (mRS 0, 1, and 2), daily living (BI scores ≥ 90), and TCM syndrome. Secondary outcome analyses will be carried out according to standard statistical principles for comparison of parametric or non-parametric distributions as appropriate. Logistical regression analysis will be used to adjust for chance imbalances in the main prognostic variables between groups, such as age, NIHSS scores, BI scores, and TCM syndrome scores.

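### Read plainly, the rule voiding data after worsening depression or interfering medication drops treatment failures from the primary comparison and conflicts with the stated intention-to-treat analysis

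*Protocol article*

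**What the plan says.** The primary outcome is binary and assessed after 8 weeks: "Efficacy defined as a decrease of 50% or more in the 17-item Hamilton Depression Scale (HAMD-17) score or clinical recovery (score < 7"). Under Statistical analysis, the two arms are compared by Pearson's chi-squared test, with logistic regression for adjustment.

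Four statements then govern a participant who does badly:

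- Withdrawal and discontinuation, dropouts: "Participants who fail to complete the study, regardless of time or reason, will be considered as dropouts". The next sentence adds: "The last recorded data for these participants will be included in data analyses".
- Withdrawal and discontinuation, invalid data: the rule is introduced as one for events that have nothing to do with the treatment, yet its list of examples goes on to "exacerbation of depression or commence medication that could potentially interfere with JDTLG, will be treated as invalid".
- Withdrawal and discontinuation, closing sentence: "Where appropriate, data collected by these participants will be used in intention-to-treat analyses".
- Statistical analysis: "Outcomes are based on the intention-to-treat analysis". No exception is attached.

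The Intervention section describes how such participants arise: "Participants can withdraw from the study and choose modern medical treatments, such as SSRI antidepressants, when their depressive symptoms worsen".

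**The concern.** Exacerbation of depression is presented as an example of an unrelated complication. It is in fact the treated condition moving the wrong way, and so failure on the primary endpoint. Starting an antidepressant because symptoms have worsened is the same failure seen by another route, and the Intervention section expects it to happen.

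If these participants' data are discarded, the analysed set is selected after randomisation on the outcome itself. Response rates in both arms then rest on the participants who did not fail in this way. The comparison is no longer protected by randomisation whenever worsening or rescue differs by arm.

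The trial is a pilot, but the Sample size calculation section says that its results will feed sample-size calculations for later studies. Inflated response rates would carry forward even if both arms were affected equally.

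**Working it through.** **Step 1: the rules applied to one participant.** Take someone who worsens at week 4, withdraws and starts an SSRI.

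- Dropout rule: in the denominator, scored on the last recorded HAMD-17.
- Invalid-data rule, read plainly: out of the analysis.
- Statistical analysis section: in the denominator as randomised.
- Closing sentence on intention-to-treat: in or out, depending on an undefined judgement of appropriateness.

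The denominator of the primary chi-squared test depends on which rule is followed, and the article does not rank them.

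**Step 2: effect of voiding.** The article supplies 80 participants, 40 per arm (Sample size calculation). It gives no response, worsening, rescue or dropout rates, and there is no stated figure to reproduce. Every rate below is an assumption. Let p be the response rate among all randomised in an arm and v the share voided, with voided participants all non-responders. Then:

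analysed rate = p / (1 − v)

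| True response, active v placebo | Voided, active v placebo | Analysed rates | Difference shown | Difference with all kept |
|---|---|---|---|---|
| 50% v 35% | 5% v 20% | 0.50/0.95 = 52.6% v 0.35/0.80 = 43.75% | 8.9 points | 15 |
| 50% v 35% | 15% v 5% | 0.50/0.85 = 58.8% v 0.35/0.95 = 36.8% | 22.0 points | 15 |
| 40% v 40% | 20% v 5% | 0.40/0.80 = 50.0% v 0.40/0.95 = 42.1% | +7.9 points | 0 |
| 40% v 40% | 5% v 20% | 42.1% v 50.0% | −7.9 points | 0 |
| 40% v 40% | 10% v 10% | 0.40/0.90 = 44.4% in both | 0 | 0 |

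In counts, the third row is 16/40 responders in each arm with 8 v 2 discarded: 16/32 v 16/38. The last row is 16/36 in each arm.

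**Step 3: effect on the test.** Trials with 40 per arm were simulated (400,000 per scenario), with equal response in both arms and an uncorrected two-sided Pearson test at an assumed 0.05 level. For response rates of 30% to 50%:

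- 5% v 20% voided: rejection rate 0.084 to 0.133.
- 10% v 10% voided: about 0.05.
- All randomised kept, voided participants counted as non-responders: 0.048 to 0.057.

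**Step 4: dependence on the non-response assumption.** If a share r of the arm is both voided and responding, the analysed rate becomes (p − r)/(1 − v). With r = p × v this equals p, and there is no bias. The figures above therefore apply where voiding picks out failures. That fits exacerbation of depression. It may not fit a drug started for an unrelated reason.

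**The case against.** Several points can fairly be made for the plan.

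- **The rules might be reconciled.** A reader might infer that they are logically incompatible. That is too strong. Only data obtained after the event might be void, with the last earlier record carried forward and everyone kept in the intention-to-treat set. Alternatively, the exclusion might be meant for a per-protocol set. Neither reading is written down, and the sentence covers data from these participants without a time limit, so exclusion remains the plainer reading.
- **The closing sentence addresses intention-to-treat.** It does, but it leaves inclusion to discretion and does not say how data already called invalid would be scored.
- **The word may mean non-response.** Under Secondary outcomes, invalid is the label for a reduction below 25% on the TCM scale. If that sense were meant, these participants would already count as failures. Here, though, the word is attached to data and not to an outcome category, so this is less likely. The wording would need changing in either case.
- **The sizes have no source in the article.** This stands. The equal-response rows also assume that worsening or rescue differs between arms, which is itself a treatment difference. If the arms did not differ in any respect, expected voiding would be equal and no systematic spurious difference would arise.
- **It is a pilot, declared not fully powered.** This lowers the confirmatory stakes but does not protect the response rates that later trials will use.

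An unseen analysis plan is no answer, because the article itself states the conflicting rules.

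**Conclusion.** The point holds as a conflict in the text with a predictable consequence. Followed as written, the invalid-data rule makes an outcome-dependent exclusion after randomisation, and neither the dropout rule nor the intention-to-treat statements resolve it. Confidence is high for the conflict in wording. It is lower for the amount of bias, which rests on assumed rates and on voided participants being non-responders.

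Within those assumptions, the distortion ranges from 15 points shown as 8.9 to 15 shown as 22.0, with ±7.9 points where response is equal. Equal voiding creates no difference between equal arms but still inflates both rates, from 40% to 44.4% with 10% voided.

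A reader might infer that the rule is bound to favour the granules. The document does not support that: if placebo loses more failures, a true benefit shrinks. A false or exaggerated benefit needs more voiding on active.

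**What to change.** For the primary analysis, delete the rule that treats these data as invalid and reconcile the paragraph with the Statistical analysis section:

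1. Keep all 80 randomised participants in the week-8 denominator.
2. Count exacerbation of depression, or starting an antidepressant, before week 8 as non-response.
3. For other potentially interfering medication, keep the participant in the denominator and use the observed week-8 HAMD-17 where available, with non-response scoring as a sensitivity analysis. The reverse order is also defensible, since the documents do not dictate either. The choice should be fixed before unblinding.
4. Confine any exclusion of such data to a per-protocol sensitivity analysis.
5. Remove exacerbation of depression from the examples of unrelated complications, and replace the discretionary intention-to-treat clause with a definite rule.

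This changes only who is analysed and how they are scored. Withdrawal and rescue treatment are untouched.

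The cost is one paragraph of wording before unblinding. Reported response rates will be lower, by several points if many participants are affected. In the first scenario above, active falls from 52.6% to 50% and placebo from 43.75% to 35%.
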